## II. STUDY INFORMATION

|                                                                                                                                                                                                                                                                                                                                                                                                                                                                                                                                                                                                                                                                                                                                                                                                                                                                                                                                                                                                                                                                                                                                                                                                                                                                                                                                                                                                                                                                                                                                                                                                                                                                                                                                                                                                                                                                                                                                                                                                                                                                                                                                                                                                                                                                                                |
|------------------------------------------------------------------------------------------------------------------------------------------------------------------------------------------------------------------------------------------------------------------------------------------------------------------------------------------------------------------------------------------------------------------------------------------------------------------------------------------------------------------------------------------------------------------------------------------------------------------------------------------------------------------------------------------------------------------------------------------------------------------------------------------------------------------------------------------------------------------------------------------------------------------------------------------------------------------------------------------------------------------------------------------------------------------------------------------------------------------------------------------------------------------------------------------------------------------------------------------------------------------------------------------------------------------------------------------------------------------------------------------------------------------------------------------------------------------------------------------------------------------------------------------------------------------------------------------------------------------------------------------------------------------------------------------------------------------------------------------------------------------------------------------------------------------------------------------------------------------------------------------------------------------------------------------------------------------------------------------------------------------------------------------------------------------------------------------------------------------------------------------------------------------------------------------------------------------------------------------------------------------------------------------------|
| Purpose of Study                                                                                                                                                                                                                                                                                                                                                                                                                                                                                                                                                                                                                                                                                                                                                                                                                                                                                                                                                                                                                                                                                                                                                                                                                                                                                                                                                                                                                                                                                                                                                                                                                                                                                                                                                                                                                                                                                                                                                                                                                                                                                                                                                                                                                                                                        |
| 
Alzheimer Disease (AD) is the most common cause of dementia, accounting for between 60% and 80% of all dementia cases and the sixth leading cause of mortality in the US [1]. AD associated mortality is estimated to exceed that of breast and prostate cancer combined according to the American Alzheimer's Association [1]. AD affects 46 million people worldwide, with its incidence increasing among the population above 65 years and doubling every five to ten years [2,3]. Likewise, the prevalence of the disease increases exponentially with age, rising from 11% among those 65-74, to almost 50% among those 85 or older [2]. Alzheimer disease also can occur in an early onset presentation in young adults, but this only accounts for less than one percent of the cases [4].
 
In the United States, an estimated of 5 million people over the age of 65 years are affected by AD and it is projected to rise to 13.8 million in the United States and more than 131 million worldwide by 2050 (a proportionate increase of 250%) [1,3,5]. It means that every 20 years the number of people living with dementia will double. Despite the huge healthcare and economic impact of AD, there is still no disease modifying therapeutics available. In fact, the available therapeutics show low efficacy at best in the treatment of cognitive impairment in dementia. Development of a non-invasive medical device that is effective in slowing cognitive impairment is not only revolutionary but also possibly cost- effective.
 
Information processing in the brain is thought to occur through synchronized neuronal activity in the form of network oscillations. Activity in the 30-100 Hz range is considered gamma-band oscillation and has been reported to be critical for attention, memory formation, and recall. Disruptions of gamma oscillations, particularly in the 30 – 50 Hz range, are reported as a potential early hallmark of Alzheimer's disease. Our lab previously showed a reduction in 40 Hz gamma power in several Alzheimer's mouse models. Using a non-invasive light (LED) flickering at 40 Hz, we were able to show entrainment of 40 Hz gamma oscillations in the visual cortex along with microglia activation and a
 |

significant reduction in amyloid load.

In our initial pilot study (IRB#1712179268), we found that our light and sound device is safe to use in cognitively normal adults and stimulation at 40Hz can be used to entrain their brain activity. During the pilot study, it was determined that 100% of healthy older adults (55 – 75 years old) entrained to visual stimulation, 72% entrained to auditory stimulation, and 100% entrained to a combination of light and sound stimulation. During these trials, subjects reported positive effects including that they felt calmer, more energetic and that the device was easy to use over a two-week period. No negative effects including headaches, seizures or changes in hearing and vision or unexpected side effects were reported from procedures or prolonged stimulation. In anticipation that subjects may experience mild eyestrain, subtitle size was increased on the tablet fixed to the device to aid in ease of reading the subtitles presented during the videos in this study.

The purpose of this next study is to determine whether gamma entrainment through non-invasive 40Hz sensory stimulation is possible in association cortices of subjects with mild AD as measured by electroencephalogram (EEG) during an acute stimulation session. Additionally, we aim to identify the percent of the study population who successfully entrain to each stimulation condition. This study will provide critical insight into potential longitudinal studies involving non-invasive 40Hz sensory stimulation in subject with AD as a possible therapeutic strategy for AD.

3. World Alzheimer Report 2015: The Global Impact of Dementia <http://www.alz.co.uk/research/world-report-2015> (Accessed on October 26, 2017) [L] [SEP]

## **Experimental Procedures**

Prior to the arrival at MIT for this study, each subject will be sent a copy of the informed consent document and the research coordinator will go over inclusion and exclusion criteria by phone. All recruited subjects will be required to bring a family member or a legally authorized representative to their visit and be present during the consenting process.

Subjects will be evaluated in the Martinos Imaging Center at MIT's McGovern Institute. Before initiating any study procedures, each subject will also be screened to determine whether he/she has the capacity to consent. To assess capacity, a board certified MD will ask some questions to evaluate the patient's decision-making ability. In brief, we will assess understanding, the patient's choice, their appreciation of how this trial applies to the patient, and their ability to compare and infer the consequences of their participation in our study. To assess understanding, we will ask, "Can you tell me in your own words what I just told you about our trial using light and sound to treat dementia?". To see if they have the ability to make a decision, "Based on what we just discussed about the trial, what do you choose?". To see if the patient understands how this applies to him/her, "Regardless of what your choice is, can you tell me how you think this trial may benefit or harm you?". And to understand the patient's ability to reason, "How will this trial affect your daily life?". The MD will pay attention to the logical

## **#1902706647, Acute Treatment of Alzheimer's disease with Gamma Frequency Stimulation**

consistency of the choice based on the reasoning provided. Patients with MMSE > 24 usually have capacity to make medical and health decisions but will be evaluated by the MD as described above. If the subject has capacity, he/she will sign the consent form. If the subject does not have capacity, then both the subject and the caretaker will be required to sign the consent form.

Before their arrival, all subjects will be randomized into one of two groups in a 1:1 ratio for the 60-minute stimulation session described below (step 6). Group 1 will receive 60 minutes of the treatment: light flickering at 30 – 50Hz and sound between 30 – 50 Hz. Group 2 will receive 60 minutes of the control: constant light and white noise. Subjects will not be informed which group they have been randomized to.

1. All subjects will undergo cognitive and mental health evaluations. They may be asked questions from the Mini-Mental State Exam (MMSE), the Alzheimer's Disease Assessment Scale – Cognitive Subscale test (ADAS-Cog), and/or the CCAS Schmahmann scale to evaluate their cognition. They will also complete modified forms from the National Alzheimer's Coordinating Center Uniform Data set. This set includes basic demographic and health questionnaires, as well as the Functional Assessment Scale (FAS), Geriatric Depression Scale (GDS) and the Clinical Dementia Rating (CDR). These questionnaires are attached for your review. These assessments may take 60-90 minutes to fill out with one of our team members. Additional memory tests may also be administered.
2. Subjects will then have their brain waves recorded by electroencephalogram (EEG). This is done by first placing the EEG cap on their heads with EEG electrodes that touch their scalp using a water-soluble gel. The process of putting the EEG cap on takes 15 -30 minutes to complete.
3. Then, video recording of the subject will start and the subject will be asked to sit quietly with their eyes open for 2 minutes as their brain waves are captured by the EEG machine. The subject will then be asked to close their eyes for another 2 minutes to allow for the EEG to record their brain activity with eyes closed.
4. All subjects will receive various combinations of visual, auditory and tactile stimulation, which includes stationary (e.g., constant light, white noise and/or no touch with no vibration) and non-stationary (e.g., a. visual: light flickering at 0.1 - 4Hz and 30 50Hz, b. auditory: sound clicks between 0.1 4 Hz and 30 -- 50 Hz and c. tactile: vibrations between 0.1- 4 Hz and 30 -- 50 Hz) using the devices described below for up to 1.5 hours. The subject will be asked to watch the light panel or monitor from which the light is flickering, listen to the sounds that will be audible throughout the room, or interact with the tactile stimulation (vibration) device. The subject will be asked to either keep their eyes open or closed for short periods. The characteristics of the stimulation other than the frequency (e.g., intensity, duration, addition of a tablet device for entertainment) may also be altered. The upper limit of light intensity used will be 800 lux and the longest duration of treatment time is 60 minutes. Each stimulation period will last 1 5 minutes and be preceded by a baseline period during which the light is obscured and the sound volume is turned off. The order in which each of these stimulation conditions is presented will be randomized. The last stimulation condition will be followed by a baseline period in which the light is obscured and the sound volume is turned off. The characteristics of the stimulation other than the frequency (e.g., intensity, duration, addition of a tablet device for entertainment) may also be altered. The upper limit of light intensity used will be 800 lux and the longest duration of treatment time is 60 minutes. Each stimulation period will last 1 – 5 minutes and be preceded by a baseline period during which the light is obscured and the sound volume is turned off. The order in which each of these stimulation conditions is presented will be randomized. The last stimulation condition will be followed by a baseline period in which the light is obscured and the

sound volume is turned off.

5. The subject will then complete one final 60-minute stimulation session using either the nonstationary bimodal (i.e., simultaneous 30 – 50 Hz auditory and 30 – 50 Hz visual) or the stationary bimodal (i.e., simultaneous white noise and constant light) stimulation depending on their randomization assignment. During the 60 minutes, the subject will be instructed to keep their eyes open and watch a tablet that will be attached onto our device and playing a video clip or a slideshow of photos. Cognitive, mental, and memory evaluations from 1 above may be repeated at the conclusion of the stimulation.

Subjects will be awake during the entirety of the study assessments. An attention button or other queue may be used to intermittently assess if subjects have fallen asleep during the stimulation regime. Visual and auditory stimulation devices will be programmed to control for intensity, frequency of operation, and fail-safes in case of subject duress.

We anticipate approximately 1.5 hours total for the behavioral portions (i.e., cognitive and mental health evaluations) and 2 hours total for the stimulation + EEG sessions for each subject.

*A board certified MD will be present during the study procedures. In the event a subject experiences discomfort, anxiety, seizure, or any other adverse event, the following protocol will be followed:*

1. *The stimulation or testing will be stopped immediately.*
2. *A research assistant will immediately call Emergency Medical Services (EMS) from a MIT phone by dialing 100 or from a cellphone by dialing [name]*
3. *A trained member of the team will monitor the subject and if deemed necessary administer basic life support and/ or obtain vital signs including blood pressure, heart rate and pulse oximetry until emergency staff arrive.*
4. *A trained responder will arrive at the scene to determine if MIT medical is an appropriate venue for the subject to receive care or if the subject should be transported to a hospital.*
5. *Once the subject's safety has been insured, investigators will complete the Adverse Event/Unanticipated Problem Reporting Form. If the event is severe or unanticipated, this form will be submitted within 48 hours of the event occurrence. All other adverse events will be submitted within 10 working days.*
6. *In the event of an adverse reaction, the team certified MD would make the decision along with the subject and their designated family member or legal representative if the study will be safe to continue. If the event was considered serious or unexpected and continuing research protocol may pose a danger to their health, it is possible that they will be removed from the study for their safety.*

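### On the in-person route, allocation is set before arrival but not used until step 5, so losses from consent, evaluation and step 4 fall after randomisation and staff knowledge of the arm is not ruled out

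*Protocol*

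**What the plan says.** Before an in-person visit the protocol provides for two things besides randomisation (Experimental Procedures, opening paragraph): the consent document is sent out, and "the research coordinator will go over inclusion and exclusion criteria by phone". The group-assignment paragraph then fixes the allocation at the same stage: "Before their arrival, all subjects will be randomized into one of two groups in a 1:1 ratio for the 60-minute stimulation session". It adds that subjects will not be told their group. It does not mention staff, who holds the list, or concealment.

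The rest happens on site. A companion is "required to bring a family member or a legally authorized representative to their visit and be present during the consenting process". On capacity: "Before initiating any study procedures, each subject will also be screened to determine whether he/she has the capacity to consent". On signing: "If the subject has capacity, he/she will sign the consent form"; if capacity is lacking, "then both the subject and the caretaker will be required to sign the consent form". Step 1 follows: "All subjects will undergo cognitive and mental health evaluations". Steps 2 to 4 cover the EEG cap, the resting recordings and up to 1.5 hours of short stimulation conditions that every subject receives in random order. The two groups first differ in step 5, the 60-minute session. The group-assignment paragraph cites that session as step 6, but the procedure list ends at step 5.

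The COVID-19 Cohort section has a different order: consent, then virtual cognitive testing, then notice of whether the criteria are met, and only then the campus visit. It does not say where randomisation falls.

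**The concern.** Randomisation protects a comparison only from the moment of allocation, and only if those who drop out afterwards do so for reasons unrelated to the arm. Here several hurdles stand between the allocation and its first use. A subject who declines, is found ineligible or stops in step 4 has already been assigned but never receives the assigned session.

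If the person handling one of these decisions knows the arm, the losses can differ by arm. Step 4 gives the clearest mechanism. Everyone is exposed to flicker there, and the adverse-event procedure lets the physician, with the subject and family, decide whether to go on. For a subject who was uncomfortable, going on means an hour of flicker in Group 1 and an hour of constant light in Group 2. Someone aware of the arm could decide differently in the two cases, leaving Group 1 with fewer flicker-intolerant subjects.

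Baseline scoring is also exposed. The step 1 tests may be repeated after the session, so a rater aware of the arm could affect a before-and-after comparison from its starting point. Even losses unrelated to the arm erode the 1:1 ratio and the numbers reaching the session.

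**Working it through.** The protocol shown gives no sample size, dropout rate or between-group effect, so there is no figure to reproduce. The check is mainly one of order.

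**Order as written, in-person route**

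| Stage | When | Can a subject be lost here? |
|---|---|---|
| Consent form sent; criteria reviewed by phone | before arrival | yes; order relative to allocation not stated |
| 1:1 allocation | before arrival | – |
| Capacity check | on site | not in itself: the caretaker co-signs |
| Signed consent | on site | yes, by refusal |
| Step 1 evaluations | on site | yes, if they show ineligibility (inferred) |
| Steps 2–3, EEG set-up and resting recordings | on site | yes, by withdrawal |
| Step 4, short stimulations | on site | yes, by withdrawal or removal |
| Step 5, 60-minute session | on site | allocation first used |

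The inference for step 1 rests on two places. The stated purpose defines the population as mild AD, and the COVID-19 Cohort section makes the invitation to the EEG visit depend on meeting the criteria after cognitive testing. No sentence says that step 1 decides eligibility on the in-person route.

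**COVID-19 cohort.** Consent and eligibility testing come before the campus visit, so an allocation made before arrival could follow both. Step 4 still lies between allocation and use.

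**Illustrative size.** Assume a normal outcome and removal of the lowest fraction p of one arm only, ranked on the outcome itself. The shift of that arm's mean, in SD units, is φ(z_p)/(1 − p), where φ is the standard normal density and z_p its p-quantile.

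- p = 0.05: 0.1031/0.95 = 0.109
- p = 0.10: 0.1755/0.90 = 0.195
- p = 0.20: 0.2800/0.80 = 0.350

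If exclusion follows a score that is bivariate normal with the outcome with correlation r, the shift is multiplied by r. At p = 0.10, r = 0.5 gives 0.5 × 0.195 = 0.098 and r = 0.3 gives 0.3 × 0.195 = 0.059. If exclusions are unrelated to the arm, the expected between-group shift from this source is zero. The fractions and correlations are assumptions; the protocol supplies none.

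**The case against.** The strongest reply is that an early allocation need not be a known one. The protocol does not say that the physician, the testers or the coordinator see the list. If they do not, early randomisation costs numbers and balance but does not create this selection bias. That stands. A reader might infer that concealment fails and that baseline scores are taken with the arm known; the text supports only that neither is guarded against.

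Three further points limit the finding.

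- A reader might count subjects who lack capacity as losses. The protocol contradicts this, since they continue with a second signature.
- The phone review and the advance copy of the consent form will bring out some refusals and ineligibility before the visit. They do not replace on-site consent or the evaluations, so they reduce the losses without removing them.
- The stated aims are whether entrainment is possible in mild AD and what percentage entrain to each condition. The percentages can be obtained from step 4, where all subjects receive the conditions whatever their group. The text shown names no between-group endpoint, and repeat cognitive testing is optional. This rules out treating the point as a threat to the whole study.

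None of these answers the order itself for the 60-minute session, which is the only between-group contrast described and the only use of the 1:1 allocation.

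**Conclusion.** The point holds for the between-group comparison of the 60-minute session. On the in-person route the stated order places consent, the step 1 evaluations and step 4 after allocation, and nothing in the document corrects that. In the COVID-19 cohort only step 4 losses clearly apply.

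What is shown is an unprotected allocation, not a demonstrated bias. Bias requires that someone influencing the losses or the baseline scores knows the arm, which is possible but not stated. Its size cannot be derived from the document. The shifts of 0.11, 0.20 and 0.35 SD are upper bounds at their assumed one-arm exclusion rates under a normal outcome, and weaker links between exclusion and outcome give less. A must-fix grading would overstate the point. It should be fixed, because concealment lost before the session cannot be restored in the analysis and the change is small.

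**What to change.** Replace the timing in the group-assignment paragraph with: *After consent, confirmation of eligibility, the step 1 evaluations and completion of step 4, immediately before the 60-minute session (step 5), the next concealed 1:1 assignment is opened.* This also corrects the reference to step 6. State that everyone randomised at that point is analysed by assigned group, and apply the same rule to the COVID-19 cohort, whose section is silent on the timing.

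The cost is one amended sentence and a concealed list opened later in the visit, with no extra subjects or assessments. The practical drawback is that the device must be set up for the assigned arm during the visit, between steps 4 and 5. The protocol gives no reason for allocating before arrival; if there is one, such as device preparation, it should be stated. In that case the protocol should say that staff who take consent, score tests or decide on continuation do not have access to the allocation, and that all randomised subjects are accounted for by group with reasons for loss. That alternative protects concealment but leaves the losses after randomisation.
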